## Abstract

**Background:**

Breaking Free Online (BFO), a computer-assisted therapy (CAT) program for substance use disorders (SUD), has been available across UK treatment services for the past decade and has demonstrated efficacy. The Covid-19 pandemic has contributed to digital and ‘telehealth’ approaches to healthcare delivery becoming more common and accepted, and has in parallel, increased numbers of referrals to SUD services because of the impact pandemic-related stress has had on substance using habits in the general population. Digital and telehealth approaches, such as BFO, have the potential to support the treatment system to meet this increased demand for SUD services.

**Methods:**

Parallel-group randomized controlled trial of eight-week BFO as an adjunct to standard treatment for SUD, in comparison to standard treatment only, at a National Health Service (NHS) Mental Health Trust in North-West England. Participants will be service users aged 18 years and over with demonstrable SUD for at least 12-months. Interventional and control groups will be compared on multiple measures from baseline to post-treatment assessment at eight-weeks, and then three and six-months follow-up. Primary outcome will be self-reported substance use, with secondary outcomes being standardized assessments of substance dependence, mental health, biopsychosocial functioning and quality of life.

**Discussion:**

This study will examine whether BFO and telehealth support, when delivered as an adjunct to standard SUD interventions, improves outcomes for services users receiving NHS SUD treatment. Findings from the study will be used to inform both developments to the BFO program and guidance around augmenting the delivery of CAT programs via telehealth.

*Trial registration* registered with ISRCTN on 25th May 2021—registration number: 13694016. Protocol version: 3.0 05th April 2022. Trial status: This trial is currently open to recruitment—estimated to be completed in May 2023.

## Introduction

Computer-assisted therapies (CAT) provide access to interventions, such as cognitive-behavioral therapy (CBT), via the internet. CAT can widen access to treatment, be more cost-effective than in-person therapy [1, 2] and optimize treatment fidelity [3]. Meta-analyses demonstrate CAT to be as effective at reducing self-reported levels of anxiety and depression as standard in-person treatments, and superior to waiting list and active control conditions [4–7]—subsequently, CAT is recommended by the UK National Institute for Health and Care Excellence (NICE) [8].

The evidence-base for CAT for substance use disorders (SUD) has been growing for over a decade e.g. [9–11]. Accessing interventions online may overcome specific barriers to accessing SUD services including shame and stigma [12]. Breaking Free Online (BFO) is a tailorable CAT program to support recovery from SUD, which has been delivered via UK community services for the past 12-years, and in UK criminal justice services for the past eight years. And since 2019, BFO has been delivered in both Canadian community and US correctional settings. BFO can be delivered as a ‘self-help’ program or as a structured practitioner-facilitated program and contains 12 core evidence-based ‘behavioral change techniques’ (BCTs) [13], which are informed by CBT [14], relapse prevention [15], mindfulness [16], and motivational enhancement [17]. BFO has been designed to complement and augment standard treatments for SUD such as key-working, counselling and medications, and due to its digital nature, can extend access to evidence-based interventions outside of usual treatment service operating hours, which are usually Monday through Friday, between the hours of 9am and 5pm.

Research around the efficacy of BFO has demonstrated significant reductions in substance use, substance dependence, depression and anxiety, and biopsychosocial impairment, and improvements in quality of life—these studies have been conducted with people using opiates [18], cannabis [19], alcohol [20] and methamphetamine [21]. BFO studies have also been conducted in multiple treatment settings, including eTherapy ‘dual diagnosis’ mental health services [22, 23] and in UK [24, 25] and US [21] prisons. Research has also indicated that users follow tailoring advice provided by the program [26] and has also demonstrated a ‘dose response’ [19, 25, 26]. Baseline clinical characteristics of individuals engaging with the program have been demonstrated to be associated with engagement and outcomes [18, 20, 27].

A significant barrier to accessing in-person SUD services since March 2020 has been the impact of societal lockdowns to curb transmission of ‘severe acute respiratory syndrome coronavirus-2’ (SAR-CoV-2), or ‘COVID-19’. Social isolation throughout the pandemic, a known risk factor for SUD [28], may not have only potentially increased the vulnerability of individuals already living with SUD, but also increased the numbers of people with SUD. Figures published by the charity Alcohol Change UK indicate that COVID-19 has had a detrimental effect on drinking habits in the UK, with one in five individuals reporting increased alcohol consumption after the lockdown measures were introduced—this represents 8.6 million adults [29]. Studies conducted during the pandemic indicate that this increased consumption is associated with greater depression, anxiety and stress [30].

Despite the relative success of the COVID-19 vaccine roll-out in the UK, and the subsequent easing of social distancing restrictions, healthcare services appear to have been transformed for the long-term as a result of the pandemic, with providers continuing to use remote digital and telehealth approaches to deliver their services going forward [31]. This, alongside the increased numbers of people presenting to SUD treatment services because of changing substance use habits during the pandemic, mean research into the ability of digital treatment to effectively meet treatment demand is timely. A systematic review conducted before the COVID-19 pandemic demonstrated that when SUD services are delivered via telehealth approaches, they can provide an effective alternative to in-person services, especially during times when access to services is limited [32]. In addition, a study conducted during the pandemic has suggested that SUD services found telehealth approaches relatively easy to implement when in-person services were restricted, and that these approaches were important in ensuring service users could continue to access services [33]. Additionally, previous research into the efficacy of using a telehealth approach to deliver BFO prior to the pandemic suggested significant improvements in mental health and social functioning [22, 23].

This research highlights the need for substance use interventions that are able to (i) target novel illicit substance use, which may continue to rise as the pandemic runs its course, (ii) be delivered in ways that do not rely on service users accessing them via in-person appointments, which may be particularly important given the increased demand for services due to the impact of the pandemic, (iii) be rapidly upscaled in order to meet the increasing numbers of individuals seeking help for their substance use, and (iv) address the concurrent mental health difficulties that often occur alongside substance use. BFO has therefore been identified as a potential adjunct to standard treatment that may satisfy these unmet needs.

### Objectives

This study will examine the efficacy of BFO when delivered as an adjunct to standard treatment—BFO will be delivered via a telehealth model in which participants accessing the program will receive fortnightly ‘recovery check-in’ phone calls from their SUD treatment service. Outcomes for this interventional group will be compared to those of a control group receiving standard treatment only.

## Methods

### Trial design

Randomized, open-label, parallel-group, longitudinal randomized controlled superiority trial of (i) BFO delivered via a telehealth model plus standard treatment (intervention group), versus (ii) standard treatment only (active control group). This will be a comparison study of eight-week treatment periods in both the interventional and control groups.

### Study setting

This study will be conducted at a single site within an NHS Mental Health Trust in North-West England. This Trust serves approximately 53,000 service users a year, and the clinical site where the study will be conducted usually receives approximately 2400 referrals of service users with SUD annually, with approximately 1500 of these referrals receiving structured treatment. The Trust provides a range of services for people with SUD including six rehabilitation units, community outreach and young person teams, and a citywide Recovery Pathways service.

### Participants

Participants will be service users currently in treatment for SUD who meet the following inclusion criteria: (i) aged 18 years or above, (ii) experiencing problem alcohol and/or drug use for ≥ 12 months requiring treatment, as determined by clinical personnel at the service, (iii) willing to comply with an eight-week treatment program for problem alcohol and/or drug use, (iv) willing to provide outcome measures post-treatment, and at three and six-months follow-up, (v) able to read, write and communicate in the English language, (vi) willing and able to access an internet enabled device for the eight-week treatment period, (vii) willing and able to give informed consent for participation in the study, and capable of understanding and complying with protocol requirements.

Exclusion criteria are as follows: (i) under 18 years of age, (ii) participation in any other alcohol and/or drug related clinical studies within 12 months prior to date of consent, (iii) detention under the Mental Health Act, (iv) clinically significant intellectual or developmental disability which may impair ability to engage with BFO and/or complete the necessary assessment measures included in the methodology, (v) pregnancy (as self-reported), (vi) previous use of BFO to address drug or alcohol use within the past 12-months.

The projected sample size will require 61 evaluable participants in each of the two treatment groups (interventional and control) to achieve enough observed power (assuming an observed power of 0.80 with α = 0.05) with an allowance of 50% attrition at three and six-months follow-up, in order to detect a medium effect size (d ≤ 0.50). Therefore, to obtain a total of 122 evaluable participants, it is estimated that a total of 183 participants will need to be recruited and screened. These estimations have been based on previous alcohol and drug studies size samples [8], some of which have used longitudinal statistical analyses.

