### Outcomes

Outcomes data will be collected via self-report, with participants completing an online assessment containing a series of standardized psychometric measures at Baseline, End of Treatment, and 3-month and 6-month follow up timepoints. Additionally, engagement data (time spent accessing the program, number of BCTs engaged with) will be collected automatically via the BFO backend database for those participants in the interventional arm.

The primary outcome will be self-reported substance use compared to baseline following treatment completion, and at three and six-months follow-up, which will be measured using the following questions:Weekly use of primary problem substance (i.e., ‘How many days in the past week did you use [primary substance]?’‘How much [primary substance] did you use each day?’)

Secondary outcomes will be measured at corresponding time points using the following standardized measures:Severity of Dependence Scale (SDS) [37, 38]: A five-item scale measuring severity of substance dependence—internal reliability: α = 0.81–0.90; test–retest reliability ICC = 0.89.Patient Health Questionnaire-4 (PHQ-4) [39]: A four-item scale that measures severity of depression and anxiety—internal reliability, α = 0.81.Five items (1, 2, 17, 18, 20) from the World Health Organization Quality of Life scale (WHOQoL-BREF) [40]—internal reliability of these five items, α = 0.84.Recovery Progression Measure (RPM) [34, 35]: A 36-item scale measuring functioning in six biopsychosocial domains functioning that are implicated in all SUDs and recovery from SUDs—internal consistency, α = 0.89; test–retest reliability, ICC = 0.73.

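### The recruitment target of 183 does not give 122 evaluable participants at the stated 50% attrition; it gives about 92, with about 66% power rather than 80%

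*Protocol article*

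**What the plan says.** The whole justification stands in one paragraph of the protocol article, under Methods, Participants. It requires "61 evaluable participants in each of the two treatment groups", "assuming an observed power of 0.80 with α = 0.05", for a medium standardised effect of 0.50 (printed with a less-than-or-equal sign), and "with an allowance of 50% attrition at three and six-months follow-up". From these premises it concludes that "to obtain a total of 122 evaluable participants, it is estimated that a total of 183 participants will need to be recruited and screened".

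Under Outcomes, the attrition is seen to fall on visits that belong to the primary endpoint: "The primary outcome will be self-reported substance use compared to baseline following treatment completion, and at three and six-months follow-up". The article gives no other retention figure and no other inflation rule. The Discussion expects attrition to be high and retention to be harder once the check-in calls have ended.

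**The concern.** The recruitment target is presented as a consequence of the attrition allowance, but the two do not agree. If half of those recruited are lost, 183 cannot leave 122. The number 183 is exactly what results from adding 50% to the evaluable number instead of dividing that number by the fraction retained.

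The 80% power therefore rests on an evaluable sample that the plan's own attrition assumption does not deliver. A non-significant result could be read as evidence against a medium effect, when on the plan's figures an unadjusted comparison would miss such an effect about one time in three rather than one time in five.

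**Working it through.** **Inputs, all from the sample-size paragraph.** Evaluable n = 61 per arm (122 in total); power 0.80; α = 0.05; d = 0.50; attrition 50%; recruitment target 183. Equal allocation is implied by the equal evaluable numbers. Sidedness and test are not stated. I assume a two-sided comparison of two means and check the one-sided alternative in step 5.

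**1. Reproduce the 61 per arm.** By the normal approximation, n per arm = 2(1.96 + 0.842)² / d² = 2 × 7.85 / 0.25 = 62.8, so 63 (64 by the t-test). Conversely, power at 61 per arm is Φ(d√(n/2) − 1.96) = Φ(0.5 × √30.5 − 1.96) = Φ(0.80) = 0.789, or 0.782 by the t-test. The stated 61 is close enough to 63 that nothing turns on the difference.

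**2. Reproduce the 183.**
- Correct inflation: 122 / (1 − 0.50) = 244.
- Adding 50% instead: 122 × 1.5 = 183, which matches the printed figure exactly.
- Attrition at which 183 would be right: 1 − 122/183 = 0.333.

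The target therefore follows from one-third attrition, not from one half. It is 244 − 183 = 61 short of what the stated premises require.

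**3. What 183 delivers at 50% attrition.** 183 × 0.50 = 91.5 evaluable, or 45.75 per arm. The shortfall is 122 − 91.5 = 30.5 participants, 25% of the evaluable target.

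**4. Power at that size (two-sided α = 0.05).**

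| Evaluable per arm | Power for d = 0.50, t-test | Power, normal approximation | d detectable with 80% power, t-test |
|---|---|---|---|
| 61 (as stated) | 0.782 | 0.789 | 0.51 |
| 45.75 (183 with 50% lost) | 0.658 | 0.667 | 0.59 |

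The normal figure in the second row is Φ(0.5 × √22.875 − 1.96) = Φ(0.431) = 0.667. About 12 points of the gap come from the attrition step (78% to 66%). The other 2 points come from 61 per arm giving 78% rather than 80%.

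**5. One-sided check (t-test).** Power at 45.75 per arm would be 0.767, but at 61 per arm it would be 0.865, and only about 50 per arm would be needed for 80%. The stated pair of 61 per arm and 0.80 therefore fits a two-sided test.

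**6. Baseline adjustment.** With baseline–outcome correlation r, the residual SD is multiplied by √(1 − r²). At 45.75 per arm (normal approximation), power is 0.71 for r = 0.3, 0.79 for r = 0.5 and 0.92 for r = 0.7. These correlations are assumptions; the protocol gives none.

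**The case against.** The arithmetic of 244 against 183 has no good answer, but the 66% can be challenged. It is the power of an unadjusted two-sided t-test at one follow-up visit with half the data missing. The Data analysis and management section plans more than that: repeated measures ANOVA as the principal strategy, ANCOVA, regression on baseline, and mixed models fitted by maximum likelihood to all available data. The 50% is attached only to three and six months, so the end-of-treatment comparison may keep more participants. With a baseline correlation of 0.5, the adjusted analysis at 46 per arm would have about 79% power, almost the same as 61 per arm unadjusted (45.75 / 0.75 = 61).

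This stands as a limit on the 66%: it is the power on the basis the protocol itself used, not a forecast for every planned analysis. It does not rescue the paragraph, which counts evaluable participants, uses no correlation and claims no gain from repeated measures. Three and six months are also primary-outcome visits.

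It may also be said that the 50% was meant as an uplift on 122. Then 183 is arithmetically right, but the text calls the 50% attrition at named follow-ups, and an uplift of that size covers only a one-third loss. Either the number or the percentage has to change.

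Finally, the inequality sign before 0.50 and the phrase observed power are matters of wording. The target is plainly a medium effect of 0.50, and the finding does not rest on these.

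**Conclusion.** Wrong as written. The target of 183 contradicts the stated 50% attrition: 244 would be needed for 122 evaluable, or attrition would have to be about 33%. With 183 randomised and half lost, about 92 remain evaluable (46 per arm), a quarter fewer than planned. Power for d = 0.50 is then about 66%, and 80% power is reached only at d = 0.59.

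The 92 rests only on the document's figures and on all 183 being randomised. The protocol describes the 183 as recruited and screened, and under Recruitment eligibility is determined after consent and before randomisation. If the 183 include screen failures, the evaluable number falls below 92. The power figures further assume a two-sided 5% t-test, equal arms and no baseline adjustment.

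**What to change.** Keep 183 and restate what it provides, for example: *With 183 randomised and 50% attrition at follow-up, about 92 participants (46 per arm) are expected to be evaluable. For an unadjusted two-sided 5% t-test this gives about 66% power for d = 0.50, or 80% power for d = 0.59.* If the team in fact expects one-third attrition, state 33% in place of 50%, with a reason, since the Discussion anticipates high attrition.

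In the same edit, say whether 183 counts those screened or those randomised, write d = 0.50 with an equals sign, and call the 0.80 power rather than observed power. If the team wishes to count the gain from baseline adjustment, it should state the assumed correlation and its source.

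The cost is wording in the protocol and wherever the figure is repeated, and a less favourable stated power. No additional participants are needed. Holding to both 50% attrition and 122 evaluable instead would mean randomising 244, 61 more than planned.

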### Recruitment

Participants will be recruited from Greater Manchester Mental Health NHS Foundation Trust’s (GMMH’s) patient population. GMMH practitioners and clinicians will identify potential participants who may meet trial inclusion criteria, and potential participants will be provided with an approved Patient Information Sheet. If the individual wishes to enroll in the trial, a member of the research team will obtain consent from the individual, at which point eligibility will be determined prior to randomization. A member of the research team within the participating organization who is qualified by education, training or experience, will conduct informed consent procedures.

### Interventions

Participants in the intervention group will be encouraged to spend one-hour per week working on BFO for the eight-week treatment period. Online access to BFO is granted via the activation of an online account using a ‘service code’ provided by the study team. Participants must agree to a Terms and Conditions of Use when they activate their account, which is in accordance with the Participant Information Sheet and Informed Consent Form and conforms to the United Kingdom General Data Protection Regulation (GDPR).

Upon account activation, each participant will be required to complete a baseline assessment of their substance use and dependence, and their wider biopsychosocial functioning. Included in this assessment is the ‘Recovery Progression Measure’ RPM: [34, 35], which measures levels of functioning across six biopsychosocial domains. BFO then uses these data to populate a six-domain model (see Fig. 1), the ‘Lifestyle Balance Model’ LBM: [36]. The LBM acts as a clinical formulation to help the user understand the specific issues and domains of functioning that may be implicated in their substance use and provides access to the clinical content of the program (See Table 1).

**Fig. 1 Fig1:**
[figure not shown]
The Lifestyle Balance Model

Based on RPM scores, each of the domains of the LBM are colored either green, amber, or red, indicating respectively, ‘little’, ‘moderate’ or ‘significant’ impairment. Tailoring advice then guides the user to complete clinical content of the program that is able to address the domains of their functioning in the LBM where they may be experiencing the greatest levels of impairment (amber and red domains of the LBM). Individuals are able to address these domains of functioning by completing the 12 main BCTs included in the program (see Table 1). Every two-weeks BFO prompts each user to complete a mandatory ‘Progress Check’ assessment, which is comprised of the same items as the baseline assessment. Alongside providing access to the BFO program, participants will receive fortnightly 15–20 min recovery check-in telephone calls from the SUD service—a total of four telephone calls during the treatment period. Phone calls will include questions relating to the participant’s understanding and perception of the content of BFO, their ability to practice and rehearse the skills they are learning from the program, and support needs.

**Table Tab1:** The 'behavioral change techniques' (BCTs) contained within Breaking Free Online

Content in Breaking Free Online	Description of strategy	Therapeutic approaches underpinning strategies	BCT taxonomy (V1) techniques (number in taxonomy)
Baseline and progress check assessments	Monitor behavior to provide feedback about progress towards goals; Encourage new behaviors via positive feedback	Goal setting; self-monitoring	Self-monitoring of behavior (2.3); Feedback on outcome(s) of behavior (2.7)
Lifestyle Balance Model	Generic formulation; Idiosyncratic formulation; Personalized feedback; Case formulation—understand the links between situations, thoughts, emotions, behaviors, physical sensations, and lifestyle	Node-link mapping (International Treatment Effectiveness Project (ITEP); Cognitive-behavioral therapy (CBT)	Information about antecedents (4.2); Information about health consequences (5.1); Salience of consequences (5.2); Information about social and environmental consequences (5.3); Information about emotional consequences (5.6)
Difficult situations domain of LBM	Assessment; Self-monitoring; Standardized measures; Psycho-education on impact of problematic situations; Intervention to help people in distress access support; Recognize–avoid–cope; Relapse prevention for coping with environmental/situational/emotional triggers; Creating action plans on how to avoid or cope in high risk situations	All structured therapeutic approaches; Psychoeducation; Guided self-help; Relapse prevention; Refusal skills	Social support (unspecified) (3.1); Reduce negative emotions (11.2); Problem solving (1.2); Action planning (1.4); Instruction on how to perform the behavior (4.1); behavioral practice/rehearsal (8.1); behavior substitution (8.2); Avoidance/reducing exposure to cues for the behavior (12.3); Goal setting (behavior) (1.1)
Negative thoughts domain of LBM	Psychoeducation on impact on negative thoughts; Mind traps; Cognitive restructuring; Challenge thoughts that may be unhelpful	Psychoeducation; Guided self-help; International Treatment Effectiveness Project (ITEP); Cognitive-behavioral therapy (CBT)	Information about antecedents (4.2); Information about health consequences (5.1); Salience of consequences (5.2); Information about social and environmental consequences (5.3); Information about emotional consequences (5.6); Re-attribution (4.3); Framing-reframing (13.2)
Emotions domain of LBM	Psychoeducation on impact on emotions; Attention narrowing; Attention switching; Emotional regulation; Recognize/understand/normalize emotions; Developing more appropriate coping strategies	Psychoeducation; Guided self-help; Coping strategy enhancement (CSE); Mindfulness-based cognitive therapy	Information about antecedents (4.2); Information about health consequences (5.1); Salience of consequences (5.2); Information about social and environmental consequences (5.3); Information about emotional consequences (5.6); behavioral practice/rehearsal (8.1); Reduce negative emotions (11.2); Problem solving (1.2); Social support (unspecified) (3.1); behavioral practice/rehearsal (8.1); Distraction (12.4)
Physical sensations domain of LBM	Psychoeducation on impact of physical sensations; Urge surfing; Body scanning; Relapse prevention-based techniques	Psychoeducation; Guided self-help; Mindfulness-based cognitive therapy	Information about antecedents (4.2); Information about health consequences (5.1); Salience of consequences (5.2); Information about social and environmental consequences (5.3); Information about emotional consequences (5.6); Instruction on how to perform a behavior (4.1); behavioral practice/rehearsal (8.1); Reduce negative emotions (11.2)
Unhelpful behaviors domain of LBM	Psychoeducation on impact of destructive behaviors; Activity scheduling; Behavioral activation; Encourage new behaviors via positive feedback; Increase activity to increase energy levels and relieve boredom	Psychoeducation; Guided self-help; Cognitive-behavioral therapy (CBT)	Information about antecedents (4.2); Information about health consequences (5.1); Salience of consequences (5.2); Information about social and environmental consequences (5.3); Information about emotional consequences (5.6); Non-specific reward (10.3); Non-specific incentive (10.6); Reward approximation (14.4); Rewarding completion (14.5); Goal setting (behavior) (1.1); Action planning (1.4)
Lifestyle domain of LBM	Psychoeducation on impact of lifestyle; Creating SMART goals for recovery; Goalsetting Increase treatment engagement and retention. Increase readiness to change behavior	Psychoeducation; Guided self-help; Motivational enhancement therapy (MET); Implementation intentions	Goal setting (behavior) (1.1); Problem solving (1.2); Goal setting (outcome) (1.3); Action planning (1.4); Non-specific reward (10.3); Focus on past success (15.3)

